###### **List of Abbreviations**

**Abbreviation Definition**

ADHD Attention Deficit Hyperactivity Disorder

AE(s) Adverse Event(s)

AESI(s) Adverse Event of Special Interest(s)

AHRC Applied Health Research Centre

AMPA Amino-3-hydroxy-5-methyl-4-isoxazole propionic acid

APEQ Acceptance/Avoidance-Promoting Experiences

Questionnaire

API Application Programming Interface

ASC Altered States of Consciousness Rating Scale

BEAQ Brief Experiential Avoidance Questionnaire

CAPS-5 Clinician-Administered Posttraumatic Stress Disorder Scale for Diagnostic and Statistical Manual for Mental Disorders, Fifth Edition

CI Confidence Interval

CPT Cognitive Processing Therapy

CRF Case Report Form

CSSRS Columbia Suicide Severity Rating Scale

CTQ-SF Childhood Trauma Questionnaire-Short Form

DERS-SF Difficulties in Emotion Regulation Scale-Short Form

DES-II Dissociative Experiences Scale II

DPP Digital Phenotype Profile

DS-II Demoralization Scale-II

DSM-5 Diagnostic and Statistical Manual for Mental Disorders, Fifth Edition

EBI Emotional Breakthrough Inventory

eCRF Electronic Case Report Form

GABA Gamma-aminobutyric Acid

GAD-7 Generalized Anxiety Disorder Scale, 7-item

GCP Good Clinical Practice

HT Hydroxytryptamine

ICF Informed Consent Form

ICG-R Inventory of Complicated Grief-Revised

IPF Inventory of Psychosocial Functioning

IRB Institutional Review Board

MDMA 3,4-methylenedioxymethamphetamine

MINI Mini International Neuropsychiatric Interview

MPFI-24 Multidimensional Psychological Flexibility Inventory

NMDA N-methyl-D-aspartate

PCL-5 Posttraumatic Stress Disorder Checklist-5 (PCL-5)

pDPP Personalized Digital Phenotype Profile

PHQ-9 Patient Health Questionnaire-9

PID Participant Identification

PII Personal Identifiable Information

PIQ Psychological Insight Questionnaire

PMBS Posttraumatic Maladaptive Beliefs Scale

PSQI Pittsburgh Sleep Quality Index

PTSD Posttraumatic Stress Disorder

QRI Quality of Relationships Inventory

REDCap Research Electronic Data Capture

REB Research Ethics Board

RPCA Robust Principal Component Analysis

SAE(s) Serious Adverse Event(s)

SCS-SF Self-Compassion Scale-Short Form

SD Standard Deviation

SDS Sheehan Disability Scale

SID Statistics, Information Theory, Data-driven

SNRI Serotonin Norepinephrine Reuptake Inhibitor

SSRI Selective Serotonin Reuptake Inhibitor

TEAE(s) Treatment Emergent Adverse Event(s)

TRD Treatment Resistant Depression

WAI-SF Working Alliance Inventory-Short Form

WHO-5 World Health Organization Well-Being Index, 5-item

# **Study Summary**

| Name of Sponsor-Investigator:  [name], St. Michael’s Hospital | |
| --- | --- |
| Name of Investigational Product:  Psilocybin | Protocol Identification Code:  23-230 |

**ClinicalTrials.gov Number**: Not yet assigned

**Clinical Phase**: 2

| Title | Psilocybin-Assisted Massed Cognitive Processing Therapy for Chronic Posttraumatic Stress Disorder: An Open-label Trial |
| --- | --- |
| Sources of monetary or material support | Internal sources of funding |
| Brief title | Psilocybin-assisted CPT for PTSD |
| Indication: | Adults with Chronic Posttraumatic Stress Disorder (PTSD) |
| Condition(s) or focus of study | Posttraumatic Stress Disorder |
| Number of participants | 15 |
| Primary outcome | To determine the feasibility and tolerability of psilocybin-assisted cognitive processing therapy (CPT) in adults with chronic PTSD (i.e., recruitment rate, withdrawals, data completion, adherence, and number and nature of adverse events). |
| Secondary outcomes | 1. To examine the effect of psilocybin-assisted CPT on clinician-rated PTSD symptoms, self-reported treatment outcomes (e.g., depression and anxiety severity, psychological functioning, sleep quality) and putative mechanisms of change. |
| Exploratory outcomes | 1. To evaluate the effect of psilocybin-assisted CPT on digital physiological passive data collected through the use of a wearable device (Oura Ring). 2. To create a personal digital phenotype profile (pDPP) based on the wearable’s and clinical assessments’ data. |
| Safety outcome | 1. To evaluate the safety of psilocybin-assisted CPT in adults with chronic PTSD. |
| Study design | Study type: Open-label  Allocation: N/A  Intervention model: Single arm  Primary outcome: Feasibility  Phase: 2 |
| Masking | N/A |
| Date of enrollment | Start date: Upon REB Approval  End date: Dependent on REB Approval |
| Eligibility criteria | Please see full inclusion and exclusion criteria in section 3.2.2.  Inclusion Criteria:   1. Meet Diagnostic and Statistical Manual-5th edition (DSM-5) criteria for current PTSD with a duration of 6 months or longer; 2. Have a Clinician-Administered PTSD Scale for Diagnostic and Statistical Manual-5th edition (DSM-5) (CAPS-5) score of 50 or higher, indicating moderate to severe PTSD symptoms; 3. Adults between the ages of 18 and 65 (inclusive) who are capable of giving informed consent; 4. Willing to stop prohibited medications; 5. Able to understand and comply with the requirements of the study, as judged by the investigator(s); 6. Agree to video and audio recording of all study visits including therapy sessions and clinical assessments; 7. Ownership of a smartphone.   Exclusion Criteria:   1. Have a history of or a current primary diagnosis of psychotic disorder, schizophrenia, delusional disorder, borderline personality disorder, schizoaffective disorder, bipolar disorder or, dissociative identity disorder; 2. Unable to accurately and completely communicate study information, answer questions about the study, and obtain consent; 3. Have evidence or history of coronary artery disease or cerebral or peripheral vascular disease, hepatic disease with abnormal liver enzymes, or any other medical disorder judged by the investigator to significantly increase the risk of psilocybin administration; 4. First degree family history of bipolar I disorder, schizophrenia or any psychotic disorders, including bipolar disorder with psychotic features; 5. Lifetime history of substance-induced psychosis; 6. Lifetime history of substance use disorder with a hallucinogen. |
| Test products, dose, and mode of administration: | Intervention: 1 dose oral psilocybin 25 mg (5* 5 mg capsules).  Participants will receive 1 week of massed CPT including 12 CPT sessions and 1 preparatory and 1 integration sessions. |
| Follow-up: | Participants will be followed-up weekly from week 1 until 12 weeks post-treatment (weeks 2-13). |
|  |  |
|  |  |

## **2. Introduction**

### **2.1. Background and Rationale**

Posttraumatic stress disorder (PTSD) is a severe psychiatric disorder that may develop as a result of a severely stressful experience, such as interpersonal violence, combat, life-threatening accident, or natural disaster [(1)](https://www.zotero.org/google-docs/?yHsXtt). PTSD is associated with significant distress, functional impairment, health burden, and economic cost [(2)](https://www.zotero.org/google-docs/?y1VX73). The prevalence of PTSD is about 3.9% in the general population [(1,2)](https://www.zotero.org/google-docs/?ZaUF7w). In individuals who have experienced trauma, the prevalence rate is 5.6% [(2)](https://www.zotero.org/google-docs/?Gg8u0S). Women have a lifetime PTSD prevalence rate of 9.7%, compared to 3.6% in men [(3)](https://www.zotero.org/google-docs/?mjtpze). Sexual violence is the main cause of PTSD (33%), with 94% of rape victims exhibiting PTSD symptoms within two weeks after their traumatic experience [(4)](https://www.zotero.org/google-docs/?f3cdgn). PTSD symptoms include persistent intrusive recollections, avoidance of trauma-related stimuli, negative changes in cognitions and mood, and hyperarousal, as well as distressing and intrusive memories and nightmares of the trauma, irritability, hypervigilance, difficulty sleeping, poor concentration, and emotional withdrawal [(2,5)](https://www.zotero.org/google-docs/?0Hq147). PTSD is classified into two forms based on its duration: acute PTSD and chronic PTSD. Acute PTSD occurs when symptoms last less than three months; chronic PTSD occurs when symptoms last more than three months [(6,7)](https://www.zotero.org/google-docs/?xOMkVK).

There are several medications and evidence-based psychotherapies available to treat PTSD. Many patients, however, do not respond to these therapies, which puts them at risk for a chronic condition and poor long-term prognosis [(2,8)](https://www.zotero.org/google-docs/?GW9JOe). While many patients with PTSD achieve remission with or without treatment, a significant number, approximately 50%, struggle with recurrent or chronic PTSD [(9)](https://www.zotero.org/google-docs/?S1Nkus). This is comparable with the estimated 40–60% of patients who do not respond adequately to standard pharmacotherapies [(10)](https://www.zotero.org/google-docs/?EytMQe). Therefore, it is essential to investigate novel approaches as well as novel chemical compounds for the treatment of PTSD.

Although there are several evidence-based psychotherapeutic treatments for PTSD (e.g., prolonged exposure, cognitive processing therapy [CPT]), drop-out rates are relatively high, not all individuals respond to treatment, impairment persists even after remission of the diagnosis, and the onset of treatment effects is delayed [(1,11,12)](https://www.zotero.org/google-docs/?Evsxy2). To fill these gaps, massed trauma-focused interventions that provide daily treatment over the course of 1-3 weeks have been developed and show promising outcomes, including large effect sizes and high completion rates [(13–16)](https://www.zotero.org/google-docs/?g75eRb). Nonetheless, many do not respond to this delivery strategy and continue to meet criteria for PTSD [(17)](https://www.zotero.org/google-docs/?ODiOxw) and the majority of individuals (80-87%) exhibit residual PTSD and depressive symptoms post-treatment [(18)](https://www.zotero.org/google-docs/?Fyds27). Accordingly, there is a need for novel adaptations of massed PTSD treatment that may help accelerate mechanisms of change and optimize treatment outcomes [(19)](https://www.zotero.org/google-docs/?aITWfR).

Psilocybin is a 5-hydroxytryptaminergic (serotonergic) psychedelic and a non-selective serotonin 2A receptor (5-HT_2AR_) agonist that was first synthesized by Albert Hofmann in 1958 after being originally isolated from psilocybe mushrooms by him in 1957 [(20)](https://www.zotero.org/google-docs/?mpOL4o). Psilocybin was used in psychiatric research from the early to mid-1960s until it was designated a schedule 1 drug in the United States (US) in 1970 [(21,22)](https://www.zotero.org/google-docs/?5qnGXh). Research on the effects of psilocybin resumed in the mid-1990s, and it is currently the preferred compound for use in clinical research of 5-hydroxytryptaminergic psychedelics because it has a shorter duration of action and suffers from less notoriety and stigma than other similar drugs [(23,24)](https://www.zotero.org/google-docs/?q0UCMG). Extant literature investigating the use of psychedelic drugs such as psilocybin focuses on the delivery of these drugs under controlled and optimal conditions in order to produce therapeutic effects. These studies hope to harness the psychospiritual experiences that may be induced by drugs such as psilocybin and direct them into therapeutic experiences for individuals with disorders that may be difficult to treat [(25–28)](https://www.zotero.org/google-docs/?9uyuu9).

Psilocybin has a range of effects on emotion, perception, and cognition with transdiagnostic potential due to its rapid action (i.e., within one day of dosing), large effect sizes, and high response and remission rates across a variety of psychiatric disorders [(29–36)](https://www.zotero.org/google-docs/?LaiTdZ). Preliminary lines of research suggest that psilocybin may be a potentially effective treatment for PTSD [(37,38)](https://www.zotero.org/google-docs/?drepQY).

Anderson et al. (2020) conducted an open-label, pilot study using psilocybin-assisted group therapy in 18 individuals with long-term AIDS-related demoralization [(39)](https://www.zotero.org/google-docs/?lVMrjP). There was no control group. Over seven weeks, participants underwent three hours of individual psychotherapy, 12–15 hours of group psychotherapy, and one eight-hour individual psilocybin administration session (oral dose of psilocybin: 0.30-0.36 mg/kg). Feasibility of psilocybin was evaluated by recruitment and retention rates of enrolled participants. The primary outcome measure was changes in the Demoralization Scale-II (DS-II) from baseline to the 3-month follow-up. Patients were monitored for adverse events (AEs) during the dosing sessions and at subsequent clinic and remote follow-ups. The AEs noted were hypertension, anxiety/anxiety exacerbation, nausea, headache, paranoia/ideas of reference, motor agitation/restlessness, unsteady gait/ataxia, tachycardia, thought disorder, urinary incontinence, and visual changes. The results of this study indicated a significant change in demoralization from baseline to the 3-month follow-up (mean difference -5.78 [standard deviation (SD): 6.01], 90% confidence interval (CI): 0.21-0.60). Moreover, PTSD related symptoms (assessed using PTSD Checklist-5 (PCL-5)) and pathological grief (measured using the Inventory of Complicated Grief-Revised (ICG-R)) significantly improved following psilocybin administration [(39)](https://www.zotero.org/google-docs/?KHMsLX). Additionally, the mechanisms of change underlying psilocybin therapy, including reductions in avoidance [(40,41)](https://www.zotero.org/google-docs/?S5GqtA), fear extinction in mice [(42)](https://www.zotero.org/google-docs/?sSea7e), and decreased amygdala activity [(43–45)](https://www.zotero.org/google-docs/?yYw76H) show strong overlap with those essential to efficacious PTSD treatment. Considering the results of this study and psilocybin’s mechanism of action, psilocybin-assisted therapy may be a beneficial treatment for patients with PTSD.

Research on other psychedelic drugs is being examined in patients with PTSD [(46)](https://www.zotero.org/google-docs/?2BINaL). 3,4-methylenedioxymethamphetamine (MDMA) acts as both a stimulant and psychedelic and has been used in PTSD [(47,48)](https://www.zotero.org/google-docs/?IL7luV). Michell et al. (2021) conducted a randomized, double-blind, placebo-controlled phase 3 study to investigate the effect of MDMA-assisted psychotherapy in patients with severe PTSD [(48)](https://www.zotero.org/google-docs/?fQcaRi). Ninety individuals were randomly assigned to receive MDMA or placebo, along with manualized treatment that included three initial sessions of preparation therapy and nine sessions of integrative therapy. The Clinician-Administered PTSD Scale for Diagnostic and Statistical Manual of Mental Disorders, Fifth Edition (DSM-5) (CAPS-5) was used to measure PTSD symptoms as the primary outcome, and the Sheehan Disability Scale (SDS) was used to measure functional impairment two months following the final experimental session. Suicidality and AEs were monitored throughout the study. The Clinician-Administered PTSD Scale for DSM-5 (CAPS-5) score was found to be significantly and persistently reduced in the MDMA group compared to the placebo group (p< 0.001), and the Sheehan Disability Scale (SDS) total score was significantly lower in the MDMA group compared to the placebo group (p = 0.012) [(48)](https://www.zotero.org/google-docs/?N0HSlf). Mithoefer et al. (2018) conducted a randomized, double-blind phase 2 clinical trial in 26 veterans with chronic PTSD [(49)](https://www.zotero.org/google-docs/?grRt5C). Participants were randomly assigned to three different dose groups of MDMA (30 mg, 75 mg, or 125 mg) plus psychotherapy. The treatment course consisted of 18 hours of non-drug psychotherapy and 16-24 hours (2-3 sessions) of MDMA-assisted psychotherapy. The primary outcome of this study was changes in Clinician-Administered PTSD Scale for DSM-5 (CAPS-5) from baseline to 1 month after the second dosing session. Secondary outcomes were changes in depressive symptoms, sleep quality, perceived growth following trauma, personality factors and general psychological function. Seven participants received 30 mg of MDMA and seven and twelve received 75 mg and 125 mg MDMA, respectively. The average change in Clinician-Administered PTSD Scale for DSM-5 (CAPS-5) total score from baseline to 1 month following the second blinded experimental session of MDMA plus psychotherapy was -11.4, -58.3, and -44.3 for groups that received 30 mg, 75 mg, and 125 mg, respectively. The intensity of the PTSD symptoms decreased considerably in the 75 mg (p< 0.001) and 125 mg (p< 0.001) MDMA groups compared to the 30 mg MDMA group. One month after the second blinded experimental session, depressive symptoms in the 125 mg group were significantly reduced compared to the 30 mg group (mean change in Beck Depression Inventory-II score (BDI-II) -24.6 vs. -4.6) (p< 0.001). Similarly, depressive symptoms in the 75 mg group were lower than those in the 30 mg group, although this result was not statistically significant t (-15.4 vs. -4.6, p = 0.052). In terms of mean change in Pittsburgh Sleep Quality Index (PSQI) scores, the 75 mg group improved the most, followed by the 125 mg and 30 mg groups. MDMA was generally well tolerated, with the most frequently reported AEs including anxiety, headache, fatigue, and muscle tension [(49)](https://www.zotero.org/google-docs/?EEiLvf).

Taken together, preliminary studies support the safety and efficacy of psilocybin for PTSD. Psilocybin-assisted CPT for PTSD may be a cost-effective and rapid treatment that optimizes treatment for individuals with PTSD. Therefore, we plan to conduct an open-label pilot trial to assess the feasibility, tolerability, efficacy and safety of psilocybin-assisted CPT in patients with chronic PTSD.

#### **2.2. Pharmacokinetics**

Psilocybin is metabolized (dephosphorylated) in the liver and primarily transformed into the active hydroxy metabolite, psilocin, after being taken orally. As a result, psilocybin is primarily a prodrug, while psilocin is the pharmacologically active agent in systemic circulation [(50)](https://www.zotero.org/google-docs/?SEqND8). Oral psilocybin has a 50% bioavailability, and psilocin is detected in plasma within 15-20 minutes following parent compound administration [(51)](https://www.zotero.org/google-docs/?aqV9DQ). The average blood concentration of the active metabolite psilocin following oral administration of psilocybin (0.224 mg/kg) was determined to be 8.2±2.8 ng/mL after 105±37 minutes, resulting in an estimated psilocybin dose-normalized bioavailability of 52.7±20% [(50,51)](https://www.zotero.org/google-docs/?sDI6ZY).

The half-life of psilocin after oral administration of psilocybin was determined to be around 3±1.1 hours, and it is detectable for up to 24 hours after administration [(50,51)](https://www.zotero.org/google-docs/?Y9zTAX). Hasler et al. (2002) and Lindenblatt et al. (1998) found comparable but not identical results, with peak psilocin levels appearing between 80 and 105 minutes and psilocin half-life varying between 2.25 hours for 0.2 mg/kg and 2.7 hours for 0.22 mg/kg [(52,53)](https://www.zotero.org/google-docs/?xREDsg). The peak psilocin concentration was reached more gradually in some subjects than in others, suggesting that metabolism rates might vary between individuals [(50)](https://www.zotero.org/google-docs/?K1cp5y).

Eighty percent of the psilocin detected in plasma is conjugated. Psilocin (90-97%) and psilocybin (3-10%) are both detectable in human urine, both unmodified (only 3-10%) and particularly conjugated with glucuronic acid [(53)](https://www.zotero.org/google-docs/?ZI59nx). The majority of the psilocin recovered in urine is excreted after 3 hours of oral administration and is completely eliminated within 24 hours [(53)](https://www.zotero.org/google-docs/?WyOjJh). Psilocybin (as psilocin) pharmacokinetics are linear at a dose range of 0.3-0.6 mg/kg [(51–53)](https://www.zotero.org/google-docs/?nApt6A).

##### **2.3. Preclinical Pharmacology**

Psilocybin and its active metabolite psilocin directly affect a number of 5-hydroxytryptamine (5-HT) receptor subtypes without directly affecting other neurotransmitter systems. Psilocybin’s potential for use in treatment resistant depression (TRD) treatment lies in its ability to modulate 5-HT receptors. As a 5-HT_2AR_ agonist, the downregulation of 5-HT_2A_ receptors produces antidepressant and anxiolytic effects, which are evident in more commonly used antidepressants and atypical antipsychotics [(26)](https://www.zotero.org/google-docs/?ng5aE8). When ingested, psilocybin is metabolized by intestinal alkaline phosphatases and esterases, which rapidly dephosphorylate the alkaloid into psilocin [(31,32)](https://www.zotero.org/google-docs/?UXUVX3). The putative target of psilocin and psilocybin is the agonism of the 5HT_2_ receptor class; however, studies have confirmed that there is also affinity for 5HT_1_, 5HT_4_, 5HT_5_, 5HT_6_, 5HT_7_, Dopamine 1 and 3 receptors [(54)](https://www.zotero.org/google-docs/?7yrNNH). Psilocybin, a naturally occurring alkaloid, has been classified, along with its active metabolite psilocin, as a tryptamine [(55)](https://www.zotero.org/google-docs/?wDuML4).

The PTSD pathophysiology involves alterations in neurotransmitters such as gamma-aminobutyric acid (GABA), glutamate, serotonin, neuropeptide Y, and other endogenous opioids and neurohormonal functioning [(2,56)](https://www.zotero.org/google-docs/?rJ1Uq7). It has been proposed that 5-HT_2AR_ agonism raises extracellular glutamatergic concentrations in the prefrontal cortex [(57)](https://www.zotero.org/google-docs/?5L6qfk). Following glutamatergic modulation of amino-3-hydroxy-5-methyl-4-isoxazole propionic acid (AMPA) and N-methyl-D-aspartate (NMDA) receptors on cortical pyramidal cells, neurotrophin (i.e., brain derived neurotrophic factor) expression is upregulated [(57)](https://www.zotero.org/google-docs/?BsAb9f).

###### **2.4. Clinical Adverse Event Profile**

Psilocybin is generally tolerated well. Transient anxiety during psilocybin onset (20-100%), transient confusion or thought disorder (17-75%), mild transient nausea (15-33%), transient headache (33-75%), and transient elevated blood pressure (2-34%) or heart rate (6-8%) are the most common AEs with 20 mg to 30 mg of oral psilocybin [(58,59)](https://www.zotero.org/google-docs/?bXTxrX).

Onset of noticeable psychoactive effects typically occurs within one hour, peaks at about two hours after a dose, and loss occurs typically around six hours after the dose [(60)](https://www.zotero.org/google-docs/?icuc6I). Psilocybin reliably induces profound changes in sensory perception, emotion, thought, and sense of self, characterized by marked alterations in all mental functions, including perception, mood, volition, cognition and self-experience [(61,62)](https://www.zotero.org/google-docs/?aPKYWD). These profound changes are often referred to as mystical-type experiences which are defined as having profound and lasting personal value and spiritual significance toward which participants attributed prolonged beneficial improvements in attitudes, mood and behavior [(63,64)](https://www.zotero.org/google-docs/?Mf8JuE). Mystical-type experiences occurring during psilocybin treatment have often been observed to predict later effects on behavior and emotions [(34,63,64)](https://www.zotero.org/google-docs/?pboda4). However, in a study by Gukasyan et al. (2022) mystical experience after psilocybin dosing sessions only predicted self-reported increases in well-being, but did not predict improvement in depressive symptoms [(65)](https://www.zotero.org/google-docs/?UXvS4F).

Taken together, the safety of psilocybin should be considered in terms of benefit and risk. Within the context of psilocybin administration in a controlled setting, a participant may report visual or auditory disturbances, feelings of unreality, altered sense of time, and other changes in mood or affect. These effects are expected, and may be a necessary component of therapeutic response [(32)](https://www.zotero.org/google-docs/?o0HPa6). Investigators must follow regulatory guidance under 21 CFR 312.32(a) for AE reporting which addresses untoward medical occurrences associated with the use of a drug in humans, whether or not considered drug related. An AE can be any unfavorable and unintended sign (eg, an abnormal laboratory finding), symptom, or disease temporally associated with the use of a drug, without any judgment about causality. However, because self-reports of intrapsychic events associated with psilocybin usage may be neither unfavorable nor unintended, an investigator may not regard the self-reports as AEs but rather as an essential product attribute for therapeutic response. The reporting of psilocybin associated observations as AEs should be informed by this context.

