###### **2.6. Study Objectives and Hypotheses**

###### **2.6.1. Primary**

The primary objective of this clinical trial is to evaluate the feasibility and tolerability of psilocybin-assisted CPT in adults with chronic PTSD. Feasibility and tolerability will be determined using recruitment rates, withdrawal, data completion, adherence, number and nature of AEs. **H1**: It is hypothesized that psilocybin and study participation will be generally well tolerated with a 10% study dropout rate.

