###### **3.2. Population**

###### **3.2.1. Number of Participants**

A total of 15 participants are planned to be enrolled in the study.

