###### **3.10. Outcomes**

###### **3.10.1. Primary Outcome Measures**

Feasibility & tolerability will be measured by:

1. Recruitment rate (minimum threshold: 2-3 participants/month)
2. Withdrawal rate (maximum threshold: 20%)
3. Data completion rate (minimum threshold: 80%)
4. Adherence rate (minimum threshold: 80%)
5. Percentage of participants with AEs (maximum threshold: 20%)

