###### **4.1.6. Recording of Adverse Events**

AEs will be collected from day 1 of treatment week until the end of the study. At each visit, subjects will be asked if they have had any health problems since the previous visit. All AEs will be recorded appropriately, whether or not considered related to the investigational product. This will include AEs spontaneously reported by the patient and/or observed by the staff as well as AEs reported in response to a direct question e.g. “Have you had any health problems since your last visit?”

For each AE, the following parameters will be described: discovery (i.e., spontaneous or solicited); start; end date or ongoing; action taken with regards to investigational product; outcome if the AE caused the patient to discontinue; a statement if the AE fulfills the criteria for a SAE or not; the investigator’s assessment of the causal relationship between the event and the investigational product; intensity of the AE, i.e., mild (awareness of sign or symptom, but easily tolerated), moderate (discomfort sufficient to cause interference with normal activities), severe (incapacitating, with inability to perform normal activities); and resolution.

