###### **4.1.8. Adverse Events of Special Interest**

An adverse event of special interest (AESI) is an AE (serious or non-serious) of scientific and medical concern specific to the study drug, for which ongoing monitoring and immediate notification by the investigator to the sponsor is required. Such AEs may require further investigation to characterize and understand them.

The following events will be reported as AESI:

- Euphoric mood
- Dissociative disorder
- Hallucination
- Psychotic disorder
- Cognitive disorder
- Disturbance in attention
- Mood altered
- Psychomotor skills impaired
- Inappropriate affect
- Overdose
- Intentional product misuse

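### Section 2.4 lets investigators leave self-reported psychoactive effects out of the AE record while Section 4.1.8 makes several of them reportable AESIs, so the primary AE percentage has no fixed numerator

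*Protocol*

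**What the plan says.** Section 2.6.1 builds adverse events into the primary objective: "Feasibility and tolerability will be determined using recruitment rates, withdrawal, data completion, adherence, number and nature of AEs". Section 3.10.1 turns this into a measure, "Percentage of participants with AEs (maximum threshold: 20" per cent), but does not say whether expected effects of the dosing session count towards it.

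Three passages bear on whether such effects are counted.

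- **Section 2.4** says of supervised dosing that "a participant may report visual or auditory disturbances, feelings of unreality, altered sense of time, and other changes in mood or affect". It calls these effects expected and possibly necessary for response. It then says of self-reports of intrapsychic events that "an investigator may not regard the self-reports as AEs but rather as an essential product attribute for therapeutic response", and that AE reporting should take account of this.
- **Section 4.1.6** says "All AEs will be recorded appropriately, whether or not considered related to the investigational product". It includes events that are volunteered, observed by staff or elicited by a question.
- **Section 4.1.8** defines an AESI as an AE that requires immediate notification and continues: "The following events will be reported as AESI". The list includes hallucination, euphoric mood, altered mood and inappropriate affect. It makes no exception for the dosing session, sets no threshold of duration or distress, and does not refer to Section 2.4.

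**The concern.** A participant who describes visual phenomena and a lifted mood during the Day 3 session can be entered as having no event (Section 2.4) or as having one or more AESIs, and hence AEs (Section 4.1.8). Both entries can be defended from the text. The person deciding knows the treatment, since the trial is open-label and single-arm, and can know that the AE percentage is a primary measure with a ceiling.

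The choice is made at recording. An effect that was never entered cannot be restored, stratified or examined in a sensitivity analysis, so a later statistical analysis plan cannot repair the loss. At stake is whether the AE percentage and the description of psychological tolerability mean the same thing from one participant to the next, and whether they can inform the larger trial that this study is meant to prepare.

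**Working it through.** **Step 1. Set the rules side by side.**

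| Report during the session | Section 2.4 | Section 4.1.8 |
|---|---|---|
| Visual or auditory disturbance | may be left out as an AE | hallucination: AESI |
| Change in mood or affect | may be left out as an AE | euphoric mood, altered mood, inappropriate affect: AESI |
| Onset anxiety, confusion or thought disorder | named among the most common AEs | not listed under these terms |

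The overlap is in the first two rows. The scope of AESIs is also unsettled elsewhere: Section 2.6.4 defines them as relating to cardiac function, suicide risk and abuse liability, but the list in 4.1.8 has no cardiac or suicide term.

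**Step 2. Range of the psychoactive-event count.** The planned sample is 15 (Section 3.2.1). If the discretion is used throughout, few or no participants have such an event. If 4.1.8 is applied as written, the count follows the frequency of the effects. Section 2.4 says "Psilocybin reliably induces profound changes in sensory perception, emotion, thought, and sense of self" but gives no percentage. I take 75% to 100% as an assumption: 15 × 0.75 = 11.25 and 15 × 1.00 = 15, so about 11 to 15 participants.

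**Step 3. Effect on the 20% ceiling.** There is no plan figure to reproduce, since Section 7.2 says no formal sample size calculation was possible. The ceiling allows 0.20 × 15 = 3 participants. With X the number of participants with any AE and p the true proportion, P(X ≤ 3) = Σ C(15,k) p^k (1−p)^(15−k), for k = 0 to 3.

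| p | P(X ≤ 3 of 15) |
|---|---|
| 0.10 | 0.944 |
| 0.20 | 0.648 |
| 0.33 | 0.217 |
| 0.50 | 0.018 |
| 0.75 | 0.00001 |

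At p = 0.33 the four terms are 0.0025 + 0.0182 + 0.0627 + 0.1338 = 0.217.

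*If psychoactive effects are counted* (p of 0.75 or more), meeting the ceiling is practically impossible.

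*If they are left out*, the other AEs decide. Section 2.4 gives headache at 33–75%, nausea 15–33%, raised blood pressure 2–34% and raised heart rate 6–8%. The share with any AE cannot be below the share with headache, so at these rates p is at least 0.33 and the chance of meeting the ceiling is at most 0.217. If the four low-end rates are combined as though independent, p = 1 − 0.85 × 0.67 × 0.98 × 0.94 = 0.475 and the chance is 0.028.

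The ceiling would therefore probably be breached under either section. What changes with the section applied is the size of the percentage and which events make it up.

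**The case against.** The strongest reply is that the sections apply in sequence. Section 4.1 defines an AE as an undesirable condition, and an AESI is a type of AE. A report must therefore qualify as an AE before the AESI list or the recording rule in 4.1.6 applies, and Section 2.4 only helps with that first question. This reading is possible, but 4.1.8 does not state it. It also does not remove the problem: it leaves the numerator to individual judgement with no criterion for when an experience is unfavourable.

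Other replies limit the point, and they stand:

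- Section 2.4 is permissive. It covers only self-reports of intrapsychic events that may be neither unwelcome nor unintended. A reader might infer that distressing reactions can be dropped; the wording does not support that, because distress is unfavourable.
- A reader might treat onset anxiety (20–100%) and confusion or thought disorder (17–75%) as further counts at the investigator's discretion. Section 2.4 already calls both AEs, so they do not illustrate it.
- A reader might infer a swing from 0 to 15 of 15 participants, or that the choice of section decides pass or fail. The first takes reliable induction to mean 100%, a rate the protocol does not give. The second does not follow from the headache rate.
- Section 7.1 sets confidence-limit criteria only for adherence, data completion and withdrawal, and only tabulates AEs. The 20% ceiling stands in 3.10.1 alone.
- Psychological effects are also captured elsewhere: the altered-states scale after dosing, the collection of psychiatric status changes under Section 4, and session recordings. These sources limit the loss of information, but they do not feed the AE percentage.

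**Conclusion.** The point holds in a limited form. Sections 2.4 and 4.1.8 treat overlapping effects differently, no rule of precedence is given, and the primary AE percentage and the nature of the AEs reported depend on unblinded judgement at recording. The number of participants with a recorded psychoactive event could range from few or none to most of the 15. The upper end rests on the assumed 75–100% frequency.

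The conclusion against 20% is less sensitive. If headache alone occurs at its lowest quoted rate, the chance of meeting the ceiling is about 0.22 with every psychoactive effect left out, and close to zero with them included. The choice of section would matter more for pass or fail only if other AEs proved rarer than the protocol expects, for example a chance of 0.648 at a 20% rate. The reason to act before the first dose is that unrecorded events cannot be recovered.

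**What to change.** 1. Reconcile Sections 2.4, 4.1.6 and 4.1.8 under one recording rule, cross-referenced in all three. Remove the discretion not to record. Enter every acute psychoactive effect with the items already collected: start, end, intensity and action taken.
2. State in Section 3.10.1 which events count towards the AE percentage. Report the percentage twice: with all events, and without expected effects that resolved by Day 3 discharge with no intervention. Name the expected effects in advance. The codes for other action taken in Section 4.1.3 can identify intervention.
3. Reconcile the scope of AESI notification between Sections 2.4, 2.6.4 and 4.1.8. This is for the sponsor to settle; nothing here proposes narrowing it.

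The cost is protocol and CRF wording, with no new assessment, since AEs are already asked about after dosing on Day 3. Section 4.1.6 asks for an end date, so a clock time or a tick-box for resolution at discharge is needed to separate the two figures. The downside is a longer AE listing and a possibly less favourable percentage than Section 2.4 would give.
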